### 1.22 Justification Discussion

It is very likely that the continuing epidemic spread of **2009 H1N1 Influenza A** infection in the US will greatly increase in the fall-winter season when social interactions and climactic conditions become even more conducive to spread of influenza viruses. While reports to date suggest that healthy individuals typically have a mild illness, underlying medical conditions including immunodeficiency appear to increase risk for severe disease and even death with pandemic H1N1 (48). Thus, knowledge of the safety and immunogenicity of the **Influenza A (H1N1) 2009 monovalent vaccine** in HIV-infected children and youth is critically important to address the health care needs of this vulnerable population.

Because seasonal influenza has been shown to cause more severe illness in HIV-infected individuals compared to that typical of age-matched uninfected people (33;34), it is likely that **2009 H1N1 Influenza A** will result in significant morbidity and possibly mortality in HIV infected individuals. Morbidity may be a direct result of the influenza virus or infection may result in secondary bacterial infections or decreased adherence to the patient's antiretroviral therapy due to the severe nausea and vomiting that may occur with pandemic H1N1 illness. Prevention of infection in this population will be critical.

It is well established that seasonal influenza infection impacts children in a community before becoming widespread in adult populations. Susceptibility to disease among young populations appears even more pronounced with **2009 H1N1 Influenza A** as one third of older adults have measurable levels of serum HAI or neutralizing antibody against the **2009 H1N1 Influenza A** while young adults and children completely lack protective titers. The serologic data is consistent with the observation that the attack rate and disease severity for the virus appears to be much higher in younger populations with relative protection of those >50 years of age.

Efforts are currently underway to evaluate **Influenza A (H1N1) 2009 monovalent vaccine** in healthy children. However, HIV-1 infected children attend schools and participate in all the activities that typically put children at such high risk for infection with influenza. Protection of HIV-1 infected children and youth from **2009 H1N1 Influenza A** will require knowledge of safety and immunogenicity of these new products in this population.

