### 2.2 Secondary Objectives

1. To correlate vaccine response with baseline antibody titer.
2. To assess persistence of antibody response 6 months after Dose #2 of **Influenza A (H1N1) 2009 monovalent vaccine**.
3. To correlate immune responses with CD4+ cell count, CD4%, ARV use, plasma HIV-1 RNA concentration at the time of first immunization, and with timing of seasonal influenza vaccine.
4. To assess cell-mediated immune responses to **Influenza A (H1N1) 2009 monovalent vaccine**.
5. To describe influenza-like illness (ILI) occurring during the course of the study period, through clinic visits for all acute febrile and respiratory illnesses, including collection of respiratory specimens for determination of influenza with RT-PCR.
6. To explore factors related to HIV and its treatment that might affect the responses to H1N1 vaccinations.

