6.4. Criteria for Permanent Exclusion from Second Dose of Vaccine

If a subject meets any of the exclusion criteria described in section 4.4, Dose #2 cannot be administered. If a subject is excluded from receiving Dose #2 of **Influenza A (H1N1) 2009 monovalent vaccine**, site staff should make all reasonable attempts to request the subject return to clinic for the 7 month visit (end of study). Every attempt should be made to maintain phone contact, to monitor for safety, throughout the study period.

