6.5 Evaluation of Influenza-Like Illness (ILI)

Subjects who develop respiratory complaints including sore throat, coryza (runny nose) and/or cough in association with fever  $\geq 100.0^{\circ}\text{F}$  will be asked to come to clinic within 72 hours for an unscheduled study visit (see Appendices IA and IB). At this visit, a respiratory specimen will be collected even if fever is by report and not documented. Nasopharyngeal swabs or washes, or tracheal aspirates (for an intubated subject) are acceptable. An assay for **2009 H1N1 Influenza A virus** using RT-PCR will be performed at the core immunology laboratory in batches. Therefore, while the result will be shared with the site team once available, clinicians may opt to obtain additional specimens locally for cultures or PCR for evaluation of ILI.

**For this protocol, the following definition of H1N1 infection will be used: “Symptoms of influenza-like illness as well as a proven history, by RT-PCR, of novel influenza H1N1 infection, or, has positive influenza diagnostic testing since June 2009 (specificity to H1N1 not required) prior to study entry.”**

**If a subject experiences documented H1N1 infection, as defined above and in Section 4.23, between Step I and Step II of the protocol, the subject should NOT receive the second dose of vaccine but should continue to be seen at the scheduled study visits, and have blood collected, as per the Schedule of Evaluations.**

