Guillain-Barré syndrome (GBS) is an acute inflammatory neuropathy characterized by weakness, hyporeflexia or areflexia, and elevated protein concentrations in cerebrospinal fluid. Most persons who develop Guillain-Barré syndrome recover completely, although the recovery period may be as little as a few weeks or as long as a few years. About 30% of those with Guillain-Barré syndrome still have residual weakness after 3 years and about 3% may suffer a relapse of muscle weakness and tingling sensations many years after the initial attack. The rate of Guillain-Barré syndrome was significantly increased in individuals receiving the 1976 Swine Influenza (H1N1) vaccine at about 1 per 100,000 vaccine recipients. This has not been seen consistently with other influenza vaccines. Typically onset was within 6 weeks after vaccination. Interestingly, although vaccination rates have increased in the last 10 years, the numbers of reported cases of vaccine-associated Guillain-Barré syndrome have declined. It is unknown if the currently produced Novartis and other manufacturers, unadjuvanted and adjuvanted, **Influenza A (H1N1) 2009 monovalent vaccine** will result in the incidence of Guillain-Barré syndrome that was seen with the 1976 vaccine product as the mechanism leading to this response has not been completely elucidated.

There may be other unknown risks of participation. The risk to the fetus/infant is unknown because animal reproduction studies with the vaccine have not been conducted. There may be other unknown side effects.

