15. Respiratory specimens, including nasopharyngeal swab, nasal wash, or tracheal aspirate obtained at an unscheduled sick visit for evaluation of influenza like illness (ILI). Instructions for nasopharyngeal swab collection can be found in the MOP. All respiratory specimens will be processed, stored frozen and batched shipped to University of Colorado laboratory as per P1088 MOP and LPC. Respiratory specimens are not required for unscheduled sick visits if the subject is being assessed for possible AEs or GBS, without ILI.
16. STEP I Day 21 and STEP II Day 0 (Dose #2) visits should occur on the same day. However, if a subject comes in to clinic for Dose #2 and is found to have a reason for deferment of STEP II entry, such as fever, Dose #2 may be deferred for up to 7 days (28 days post Dose #1). Day 21 study evaluations should be completed. If the reason for deferral is ILI, a respiratory specimen should be collected. If Dose #2 is delayed beyond 72 hours, a history, physical, neurologic examination, pregnancy test should be repeated prior to administration of Dose #2.
17. If a female subject has a positive urine or serum pregnancy test (hCG) on STEP I Day 21, enrollment in STEP II should NOT be performed and Dose #2 vaccination should NOT be administered until  $\geq 14$  weeks of gestation. (See SOE, Appendix IB.)
18. Unscheduled visits are for assessment of ILI, possible Guillain-Barre syndrome or possible AEs. Subjects should be asked to return to clinic within 24 hours of development of symptoms consistent with Guillain-Barre syndrome; within 72 hours for assessment of possible adverse events other than GBS or for symptoms consistent with ILI.
19. For subjects who choose to prematurely discontinue the study, the early study discontinuation visit should occur.

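### For about six months after the Day 10 visit following Dose #2, influenza-like illness is captured only by self-report, month 7 does not ask about it by name, and the visit trigger does not clearly match objective 5

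*Combined protocol and SAP*

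**What the plan says.** **Objective.** Section 2.2, objective 5 (repeated in the Schema) is to describe ILI during the study period "through clinic visits for all acute febrile and respiratory illnesses, including collection of respiratory specimens for determination of influenza with RT-PCR".

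**Trigger.** Section 6.5 asks for an unscheduled visit within 72 hours from "Subjects who develop respiratory complaints including sore throat, coryza (runny nose) and/or cough in association with fever" at or above 100.0°F. At that visit "a respiratory specimen will be collected even if fever is by report and not documented". Appendix IA, footnote 15, adds: "Respiratory specimens are not required for unscheduled sick visits if the subject is being assessed for possible AEs or GBS, without ILI".

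**Contacts.** After Dose #2, Appendix IA has a Day 2 contact and a Day 10 visit (±3 days). The next column is the 7-month visit (±1 month, counted from Dose #1). Unscheduled visits remain open throughout, on the subject's report.

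**Month 7.** Section 6.2 says that data will be collected on GBS signs and symptoms and other serious adverse events. The targeted history in Appendix IA, footnote 2, does not list ILI. The reactogenicity interview is not marked for that visit. Under section 4.5, medications other than antiretrovirals and vaccines, which include influenza antivirals, are collected only to 10 days after Dose #2.

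**Other relevant text.** For subjects excluded from Dose #2, section 6.4 says: "Every attempt should be made to maintain phone contact, to monitor for safety, throughout the study period". On GBS after the 1976 vaccine, section 9.31 says: "Typically onset was within 6 weeks after vaccination". Section 8.221 makes HAI ≥1:40 at 6 months after Dose #2 a secondary endpoint. Sections 8.2 and 8.6 contain no ILI endpoint or analysis.

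**The concern.** A descriptive objective is only as good as its ascertainment. Most of follow-up here has no active enquiry. An illness that has resolved before anyone hears of it cannot be swabbed, and the closing visit has no prompt that would bring it to light. Two results are exposed:

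- **The ILI description.** Episodes that are not reported in time drop out of the count. The plan has no category for illness that occurred but was not sampled, so the report could not show how incomplete it is.
- **Persistence of antibody.** An influenza infection between STEP II Day 10 and month 7 can raise the month-7 titre. Sections 6.2 and 6.5 treat documented H1N1 infection between the doses as important enough to withhold Dose #2. After Dose #2 there is neither active detection nor an analysis rule.

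The same gap in contact also leaves later GBS symptoms after Dose #2 to self-report.

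**Working it through.** **1. Length of the interval without scheduled contact (Appendix IA)**

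Inputs: Dose #2 on day 21 to 28 after Dose #1 (section 5.0); Day 10 visit 7 to 13 days after Dose #2; final visit 6 to 8 months after Dose #1. Take 1 month = 365.25/12 = 30.44 days.

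- The plan's own window is reproduced: 7 ± 1 months = 6 to 8 months = day 183 to 244, nominal day 213.
- Day 10 visit: earliest 21 + 7 = day 28; nominal 21 + 10 = day 31; latest 28 + 13 = day 41.

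| Case | Final visit − Day 10 visit | Gap | Share of follow-up |
|---|---|---|---|
| Shortest | 183 − 41 | 142 days (4.7 months) | 142/183 = 78% |
| Nominal | 213 − 31 | 182 days (6.0 months) | 182/213 = 85% |
| Longest | 244 − 28 | 216 days (7.1 months) | 216/244 = 88.5% |

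This applies to subjects followed under Appendix IA. Women who become pregnant between doses follow Appendix IB and have a post-delivery visit instead. Assuming Dose #2 at 14 weeks and delivery at 40 weeks, their gap is (40 − 14) × 7 − 10 = 172 days to birth, and up to 172 + 28 = 200 days to the visit. It is shorter if Dose #2 is later.

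**2. Objective against trigger**

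| Illness | Objective 5, either feature | Objective 5, both features | Section 6.5 ILI visit and specimen |
|---|---|---|---|
| Respiratory with fever (measured or reported) | covered | covered | requested |
| Respiratory without fever | covered | not covered | not requested |
| Fever without respiratory complaint | covered | not covered | not requested |

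Section 6.5 matches the third column of the table and not the second. The documents do not say which reading of the objective is meant.

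**3. Can month 7 recover missed episodes?**

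The routes in section 6.2, the history list, the interview schedule and the medication collection period are set out above. None asks about ILI by name. An episode volunteered at month 7 could be written down as an adverse event under section 6.1 or as pertinent history, but nothing prompts for it or marks it as an unsampled ILI.

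**4. Sensitivity of the 6-month HAI proportion**

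Suppose a subject would have been below 1:40 but is lifted to 1:40 or above by an unrecognised infection. Each such subject adds 1/120 = 0.8 percentage points to the overall proportion and 1/40 = 2.5 points in an age stratum, assuming that the planned 120 and 40 are the denominators at that visit. The documents give no infection rate, so the number of such subjects is unknown.

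**5. GBS enquiry**

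Six weeks is 42 days. The last active enquiry before month 7 is 7 to 13 days after Dose #2, leaving 42 − 13 = 29 to 42 − 7 = 35 days, or about 4 to 5 weeks, to self-report. Counted from Dose #1, the same visit falls on day 28 to 41 and covers nearly all of the 42 days.

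**The case against.** The strongest defence is that symptom-triggered visits are a recognised choice for a descriptive secondary objective in about 140 subjects. ILI is not an endpoint, no test is planned on it, and the unscheduled-visit route is open to everyone throughout. Objective 5 can be read as illnesses that are both febrile and respiratory, which is what section 6.5 asks for. All of this is fair. It makes the trigger question one of wording, and it makes capture passive rather than absent. It does not shorten the gap or supply the missing month-7 question.

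Several stronger readings are tempting, and the documents do not support them:

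- **That illness with only one feature is never sampled.** Specimens are not required at visits without ILI, but they are not forbidden, and section 6.5 lets clinicians take additional local specimens for ILI. Appendix IA, footnote 18, also brings subjects in within 72 hours for possible adverse events.
- **That surveillance is weakest in fully vaccinated subjects, so ILI by doses received is biased.** The section 6.4 phone contact has no schedule and its stated purpose is safety. The 72-hour ILI route applies to all subjects, and section 8.6 plans no comparison by doses received.
- **That GBS follow-up stops before the risk period.** The period in section 9.31 starts at vaccination, so Day 7 to 13 lies inside it. Month 7 is a later scheduled contact with GBS enquiry and a neurological examination. The 24-hour return instruction and expedited reporting run throughout.
- **That a low count would be taken as protection.** The study has one arm, and the protocol proposes no such reading.
- **That most of the influenza season, or half of the episodes, is missed.** Section 1.22 says only that spread "will greatly increase in the fall-winter season when social interactions and climactic conditions become even more conducive to spread of influenza viruses". No season dates or reporting rates are given.

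**Conclusion.** The point holds as one about ascertainment. For a subject on Appendix IA there is no scheduled contact for 142 to 216 days, nominally 182 days or about 85% of follow-up. ILI capture over that time depends on timely self-report, and the month-7 visit is not set up to recover what was missed. The ILI count is likely to be too low, by an amount that cannot be derived from the documents. Intercurrent influenza can pass unidentified into the 6-month HAI ≥1:40 proportion, at up to 0.8 percentage points per affected subject out of 120.

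The GBS aspect is limited to roughly the last 4 to 5 weeks of the six-week period after Dose #2, during which detection relies on the 24-hour return instruction.

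The interval rests only on the stated visit windows. The direction of the ILI bias assumes that some episodes go unreported or are reported too late. The mismatch between objective 5 and section 6.5 depends on how the objective is read, which is itself a reason to reconcile the two. The matter is worth correcting because the objective is stated and the correction is small.

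**What to change.** 1. **Month-7 visit.** Record for every subject any ILI or positive influenza test since STEP II Day 10 that was not seen in clinic. Report these episodes separately from swabbed ones. Show HAI ≥1:40 at 6 months with and without subjects reporting such illness, as a sensitivity display. Leaving them out does not by itself estimate persistence, because subjects who become infected may differ in vaccine response. Ask the same question at the post-delivery visit in Appendix IB. This needs no new visit and is still useful for subjects already past part of the gap.
2. **Interim contact.** Have existing site staff make brief calls or send texts to all subjects between STEP II Day 10 and month 7, asking about fever, respiratory illness and GBS symptoms, with the first at about 6 weeks after Dose #2. With nominal timing the first falls on day 21 + 42 = 63. Monthly repeats on about days 93, 124, 154 and 185 make five contacts before day 213.
3. **Wording.** Reconcile objective 5 (section 2.2 and Schema) with section 6.5, so that both describe the same illnesses.

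**Cost.** A short amendment to Appendix IA, the month-7 form and the two texts; about 5 × 140 = 700 short contacts in all; and a few more swab visits. Subclinical infections would still be missed, so the persistence result would be only partly protected.

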4.4 Exclusion Criteria for STEP II

If a subject meets any of the following exclusion criteria, they should not receive Dose #2 (see section 6.4).

- 4.41 Has received a non-licensed agent (vaccine, drug, biologic, device, blood product, or medication), other than from participation in this study, since Dose #1, or expects to receive another non-licensed agent before the end of the study.
- 4.42 Use of anti-cancer chemotherapy or radiation therapy since Dose #1, new diagnosis of an active malignancy, or is immunosuppressed as a result of an underlying illness (other than HIV-1 infection) or treatment.
- 4.43 Use of glucocorticoids, including oral or parenteral steroids ( $\geq 2$  mg/kg per day or  $\geq 20$  mg total dose) for more than 2 weeks since vaccine Dose #1, or high-dose inhaled steroids ( $>800$  mcg/day of beclomethasone dipropionate or equivalent) since Dose #1 (nasal and topical steroids are allowed).
- 4.44 Has received immunoglobulin or other blood products since Dose #1.
- 4.45 Any Grade 3 toxicity or adverse event experienced by a subject unless the investigator has received protocol team approval.

- 4.46 Any Grade 4 toxicity or adverse event (other than injection site reaction or fever) that is definitely, probably or possibly related to study vaccine.
- 4.47 Any Grade 4 injection site reactions or fever experienced by a subject, unless the investigator has received protocol team approval.
- 4.48 Any Grade 4 adverse events that are definitely not or probably not related to study vaccine, unless the investigator has received protocol team approval.
- 4.49 New occurrence or new awareness of Guillain-Barré Syndrome in the subject or subject's family (parents, siblings, half siblings, or children) since Dose #1.
- 4.410 A new onset of a neurological disorder including (but not limited to) absent ankle and patellar deep tendon reflexes in both legs (all four absent) since Dose #1.
- 4.411 Disproportionate loss of strength in lower extremity or extremities, compared to the upper extremities (not thought to be related to pregnancy) since Dose #1.
- 4.412 Documented **2009 H1N1 Influenza A infection** since Dose #1 (see 4.23 for definition)
- 4.413 The subject, parent, or guardian refuses further vaccination.
- 4.414 Any new disease which the investigator judges to be clinically significant or clinically significant findings since Dose #1 that, in the investigator's opinion, would compromise the safety of the subject.

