**For this protocol, the following definition of H1N1 infection will be used:**  
**“Symptoms of influenza-like illness as well as a proven history, by RT-PCR, of novel influenza H1N1 infection, or, has positive influenza diagnostic testing since June 2009 (specificity to H1N1 not required) prior to study entry.”**

**If a subject experiences documented H1N1 infection, as defined in Section 4.23, between Step I and Step II of the protocol, the subject should NOT receive the second dose of vaccine but should continue to be seen at the scheduled study visits, and have blood collected, as per the Schedule of Evaluations.**

Antipyretics should not be routinely given in anticipation of adverse events after vaccination, but should not be withheld if symptoms occur. Antipyretics should be recorded when given.

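### The rule withholding Dose #2 after influenza reuses an entry definition that a non-PCR test between doses cannot meet, and no sensitivity analysis covers titres drawn after on-study infection

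*Combined protocol and SAP*

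**What the plan says.** Exclusion 4.23 defines H1N1 infection by two limbs. The first is influenza-like illness (ILI) symptoms with 2009 H1N1 shown by RT-PCR. The second is "positive influenza diagnostic testing since June 2009 (specificity to H1N1 not required) prior to study entry". Sections 6.2 and 6.5 repeat this definition in full.

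Three places then apply it to infection after the first dose:

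- 4.412 excludes from Step II a subject with documented infection "since Dose #1 (see 4.23 for definition").
- 6.2 withholds the second dose "If a subject experiences documented H1N1 infection, as defined in Section 4.23, between Step I and Step II of the protocol". The subject "should continue to be seen at the scheduled study visits, and have blood collected".
- 6.5 does the same for infection "as defined above and in Section 4.23, between Step I and Step II of the protocol".

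Section 6.4 makes these exclusions binding: "If a subject meets any of the exclusion criteria described in section 4.4, Dose #2 cannot be administered".

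Section 6.5 lets clinicians take their own local specimens for culture or PCR. The study RT-PCR is run in batches, and Section 3.0 says such results come only after the study is complete.

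On the analysis side, response is HAI of at least 1:40 at 21 days after Dose #1 and 10 days after Dose #2 (8.214), and again at 6 months after Dose #2 (8.221). Section 8.612 reports the proportion responding after each dose with a 90% confidence interval. The evaluable definition in 8.4 has no infection criterion. Section 8.1 names differing background exposure to the virus as something that may affect response.

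**The concern.** A test taken after Dose #1 cannot also precede study entry. The heading of Section 4.2 ties study entry to Step I, and 4.32 uses a different term for Step II. The second limb is therefore empty for on-study infection, and the mandatory rule depends on RT-PCR alone. With the study assay batched, only an optional local PCR is likely to trigger it before Dose #2 is due. Sites that follow the text would give the dose after a positive culture, and sites that follow the apparent intent would withhold it.

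The second gap is independent of the first. Among subjects with a titre, scoring a post-infection titre as vaccine response can only raise the observed rate. That is the wrong direction for 8.612, which uses the lower limit to say that response is no worse than a given value. A single-arm trial has no control group to reveal the effect. Section 1.22 expects transmission to grow over the fall and winter.

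**Working it through.** **Wording.** Take a subject with a positive local non-PCR influenza test between doses.

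1. Limb 1 fails because there is no RT-PCR result.
2. Limb 2 fails because the test came after Step I entry.
3. So 4.412, 6.2 and 6.5 are not triggered, whatever time window they set.

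**Which infected subjects stay in the analysis.** Subjects infected after Dose #2 remain evaluable. So does a subject deferred for ILI at Day 21 and dosed by Day 28 with the study swab unread (Appendix IA, footnote 16). That case arises from batching, not from the wording.

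**Exposure time before each titre.**

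- Step II Day 10: 21 + 10 = 31 days (range 21 + 7 = 28 to 28 + 13 = 41).
- 7-month visit: 7 × 30.4 = 213 days (6 × 30.4 = 182 to 8 × 30.4 = 243).
- Ratio: 213 / 31 ≈ 6.9, so 8.221 is the endpoint most affected.

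**The plan's own figure.** An exact (Clopper-Pearson) 90% interval for 90/120 is 67.7% to 81.4%, matching the 68% to 81% in Table 3. The same method gives 52.1% to 67.5% for 72/120 and 32.5% to 47.9% for 48/120. The half-width is 7.71 points in both.

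**Size of the shift.** Let r be the true vaccine-only response, a the proportion infected before the titre, and s the proportion of infected would-be non-responders who reach 1:40. If infection is unrelated to response:

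observed = r + a(1 − r)s

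The documents give none of these inputs, so all are assumptions.

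| Endpoint | r | a | s | Observed | Rise (points) |
|---|---|---|---|---|---|
| Primary, low | 0.60 | 0.02 | 0.5 | 0.604 | 0.4 |
| Primary, high | 0.60 | 0.10 | 1 | 0.640 | 4 |
| 8.221, low | 0.40 | 0.10 | 0.5 | 0.430 | 3 |
| 8.221, high | 0.40 | 0.30 | 1 | 0.580 | 18 |

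**Attack rate at which the rise equals the half-width:** a = 0.0771 / ((1 − r)s).

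- Primary: about 19% (s = 1) to 39% (s = 0.5), within about 31 days.
- 8.221: about 13% (s = 1) to 26% (s = 0.5), over about 7 months.

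**Do two supplementary estimates bracket the truth?** Let (a) exclude post-infection titres and (b) count them as non-response. Take N = 120, all with a titre, and every infected subject reaching 1:40.

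| Case | True | All subjects | (a) | (b) |
|---|---|---|---|---|
| Primary, 12 infected, unrelated to response | 60% | 64.0% | 60.0% | 54.0% |
| Primary, all 12 in non-responders | 60% | 70.0% | 66.7% | 60.0% |
| Primary, all 12 in responders | 60% | 60.0% | 55.6% | 50.0% |
| 8.221, 24 infected, unrelated | 40% | 52.0% | 40.0% | 32.0% |

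The true value lies between (b) and the all-subjects estimate, inclusive, in every row.

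The bracket does not extend to subjects who lose Dose #2. Suppose 12 have it withheld and 65 of the other 108 respond, giving 60.2%. Had all 12 responded to two doses, the rate would be 77/120 = 64.2%. Had none, it would be 65/120 = 54.2%.

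**The case against.** The entry phrase looks like a drafting carry-over. The operative rules carry their own window, and a sensible site would take only the type of evidence from 4.23. Because 4.23 also opens with the entry restriction, strict literalism could void the RT-PCR limb too. There are backstops: 4.414 covers "Any new disease which the investigator judges to be clinically significant or clinically significant findings since Dose #1" that would compromise safety, 4.45 covers "Any Grade 3 toxicity or adverse event experienced by a subject unless the investigator has received protocol team approval", and 6.31 to 6.33 defer the dose. Nothing in the documents shows that a second inactivated dose after influenza is harmful. On the analysis, this is a descriptive Phase II study with no success threshold. ILI with RT-PCR will be described anyway, 8.62 allows further predictors, and estimate (b) can miss the truth by more than the planned estimate does.

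Much of this stands. The intent is clear, no harm from the extra dose is shown, and the primary shift is small. The assumed primary range is also generous: detected between-dose cases leave the evaluable set, and an infection just before the draw may not yet have raised the titre.

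It does not remove either point. That a still stricter reading would disable the rule altogether is a further reason to fix the text. The backstops are discretionary, can be waived by the team, or only defer. Describing ILI and exploring predictors do not amount to a prespecified sensitivity analysis. Estimate (b) is offered only as a lower bound beside the retained all-subjects figure.

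**Conclusion.** Both points hold and should be fixed. The definition is wrong as written for on-study use: it misses infections shown only by a local non-PCR test and invites sites to differ. The consequence for dosing is minor.

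The analysis gap is minor for the primary endpoint: 0.4 to 4 points against a 7.7-point half-width. It is moderate at most for 8.221: 3 to 18 points, where infection over about seven months could be read as vaccine persistence. These sizes rest on assumed attack rates of 2–10% and 10–30%, true response of 60% and 40%, 50–100% of infected would-be non-responders reaching 1:40, and infection unrelated to response. Confidence is medium because the documents supply none of these values.

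**What to change.** **Definition.**

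- Leave 4.23 as the entry criterion.
- In 6.5, replace the repeated entry definition with an on-study one: ILI symptoms with 2009 H1N1 proven by RT-PCR, or any positive influenza test whether or not specific to H1N1, on a specimen collected since Dose #1.
- Point 4.412 and 6.2 to it, delete the entry definition repeated in 6.2, and remove the reference to 4.23 from the rule in 6.5.

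**Analysis.**

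- Keep the all-subjects estimates in 8.612 and for 8.221.
- Using the batched RT-PCR and any local positives, add estimates (a) and (b) and report how many subjects are affected.
- State that (b) and the all-subjects estimate bracket the vaccine-only rate only among subjects who have the relevant titre, and only for detected infections.
- Report subjects with Dose #2 withheld separately, with the titres still drawn at their scheduled visits.

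**Cost.** One definition, three changed cross-references and about three sentences in 8.6; specimens and assays are already planned. Some subjects with non-H1N1 influenza will lose Dose #2 and leave the evaluable set, which follows from the protocol's own choice not to require specificity. Estimate (a) conditions on a post-vaccination event, and (b) is conservative. Infections without a swab stay undetected, and the wording change does not help where only the batched study swab was taken.
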